#### Follow up data one year after the consultation

Additional measurements will be made one year following the recruitment of the final patient for each practice. Each practice will be sent a list of all recruited patients and asked to provide details of the length of each index consultation, and information on the total number of consultations and the number of consultations for RTI, for the one-year period following each patient's recruitment. To facilitate the collection of data from the practice records the study team will provide practices with support on obtaining consultation length data from their computer system, and beginning and end dates for each one-year follow-up period. General practices will be asked to include information about consultations occurring in other locations (out-of-hours, hospital, out-of-area, etc.) as well as consultations within the general practice.

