### Analysis

Statistical analyses will be conducted using SPSS, STATA, and MLwiN. The primary analysis will be intention to treat and will compare the proportion of patients who re-consulted for the same illness during the fourteen days following recruitment, in the intervention and control arms of the study. A two-level logistic model will be fitted to account for individual and practice-level factors.

Secondary outcomes include: proportion reporting having received a prescription for an antibiotic, proportion reporting having used antibiotics, parental enablement, parental satisfaction, parental assessment of the usefulness of any information received in the consultation, perceived reassurance, and the number of consultations for respiratory tract infections over the following year. These will be analysed using either two-level logistic or linear regression models as appropriate.

We will explore whether a three-level model to control for practitioner factors improves the fit of the model for each analysis.

No formal sub-group analyses are planned. However, exploratory analyses will be conducted of the impact of child's age, presenting symptom complex, and socio-economic background (using postcode of residence) on the effectiveness of the intervention.

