## Conclusion

This study aims to evaluate the effect of a booklet developed specifically for use within consultations involving children with RTIs, on re-consulting for the same illness episode and antibiotic prescribing. We will determine whether changes in antibiotic use and re-consultation are achieved at the expense of patient satisfaction, and will determine whether the interactive booklet enhances patient enablement. We will evaluate the effect on medicalisation over the subsequent year. If this intervention is found to be effective, even small changes for the commonest acute consultation could have major effects on help seeking behaviour and free up consultations in primary care for other conditions. If not effective, resources spent on developing, printing, and distributing leaflets and booklets on respiratory tract infections in children can be re-directed, and the research agenda can be re-focussed. We believe that this is the first evaluation of the use of written material on respiratory tract infection in children during the consultation.

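### The one-year RTI count contains the 14-day primary-outcome window, so on its own it cannot show a change in later consulting

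*Protocol article*

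**What the plan says.** - **Primary outcome** (Analysis): "the proportion of patients who re-consulted for the same illness during the fourteen days following recruitment", compared between arms.
- **One-year outcome** (Analysis): a secondary outcome, "the number of consultations for respiratory tract infections over the following year".
- **Window and data request** (Follow up data one year after the consultation): practices are asked for the total number of consultations and the "number of consultations for RTI, for the one-year period following each" patient's recruitment, so the year starts at recruitment. The study team sends practices the "beginning and end dates for each one-year follow-up period". Care outside the practice is to be included.
- **Two-week interview** (Follow up data collection two weeks after the initial consultation): parents report contacts with primary, secondary and out-of-hours care since enrolment.
- **Intended reading**: the Conclusion says "We will evaluate the effect on medicalisation over the subsequent year". Under Outcome measures, the Discussion lists consulting for similar illness over the following year as an outcome apart from same-illness re-consultation.

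**The concern.** Both clocks start at recruitment. A re-consultation for the index illness in the first two weeks is normally an RTI consultation, so it counts towards the primary outcome and, if it reaches the notes, towards the one-year count as well. Nothing in the stated window or data request sets the index episode aside.

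The one-year result is meant to say something further: whether families consult less for later illnesses. If the booklet works only within the index episode, the one-year estimate still moves in its favour, and a reader could credit it with a lasting change in help-seeking. The error can also run the other way. A gain in the first fortnight could offset a later rise in consulting. That matters because the Discussion raises possible adverse effects and cites a trial of a childcare booklet in which parents in the intervention arm felt less confident and knowledgeable.

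**Working it through.** **1. The planned effect.** The article gives no figure for the one-year count, so the input is the effect in Sample size estimation: 20% to 10%, 80% power, 5% significance. The usual two-proportion formula, two-sided and with continuity correction, gives 219 per arm, or 438, which is the article's figure for an individually randomised trial.

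**2. Shift in the one-year count.** Write the expected count as a days 1-14 part plus a later part, and set the later part equal in both arms. Let r be the mean number of index-illness visits per re-consulting child, taken as equal in both arms; r is at least 1.

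Difference = 0.10r - 0.20r = -0.10r, so the fall is at least 0.10 per child, provided the visits are recorded. If the count started at day 15, the expected difference would be 0.

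**3. Relative size.** The yearly RTI mean is not in the documents and is assumed. On a yearly mean of 1 to 2, the fall is 0.10/1 = 10% to 0.10/2 = 5%. Building the control mean as later mean + 0.20:

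| Assumed later mean | Control | Intervention | Ratio |
|---|---|---|---|
| 0.5 | 0.7 | 0.6 | 0.86 |
| 1 | 1.2 | 1.1 | 0.92 |
| 2 | 2.2 | 2.1 | 0.95 |
| 3 | 3.2 | 3.1 | 0.97 |

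**4. Chance that this alone reaches significance.** From the article: 60 practices, ICC 0.04 (given for re-consultation and assumed here for the count), N = 524 to 600. The design effect is 1 + (N/60 - 1) x 0.04, which is 1.309 at 524 and 1.36 at 600. The effective size per arm is 524/(2 x 1.309) = 200 and 600/(2 x 1.36) = 221. The SD is assumed to lie between sqrt(mean) and sqrt(2 x mean). SE = SD x sqrt(2/n), and the chance of a significant reduction is Phi(0.10/SE - 1.96).

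- Example, later mean 1, SD = sqrt(1.2) = 1.095, n = 221: SE = 0.104, 0.10/SE = 0.96, chance = Phi(-1.00) = 16%.
- Later mean 0.5: 13-24%. Mean 1: 9-16%. Mean 2: 7-11%. Mean 3: 6-8%.

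These are chances of a significant result in the direction of a reduction, so the no-difference benchmark is 2.5%. Adding the opposite tail moves the whole range only from 6-24% to 7-24%.

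**5. Cross-check with a negative binomial count.** With 200 per arm, SE = sqrt(2(mu + mu^2/k)/200), mu from 1 to 2 and k of 1 or 2, the SE runs from 0.12 to 0.245. A shift of 0.10 is then 0.41-0.82 SE, and the total two-sided rejection probability is 6.9-12.9%, against 5%.

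**6. Masking.** With r = 1, a later rise of 0.10 consultations per child in the intervention arm would cancel the fortnight's gain exactly, and the one-year difference would have expectation zero.

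**The case against.** The strongest reply is that the outcome is defined as total RTI consulting. The abstract, the Main research questions and the Analysis all speak of RTI consultations over the year and do not restrict them to new illnesses. The article also gives a workload rationale, for which a total from recruitment is the natural intention-to-treat measure. On that definition a fall of 0.10 per child is a real effect, and the percentages above are power, not false-positive rates. This stands. A reader might infer that the fall is spurious and that the type I error of the outcome as defined is inflated; the article does not support that. The fault is confined to reading the total as later behaviour.

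A reader might also infer that the overlap can never be removed. That goes too far. The two-week interview records contacts in the same fortnight, and the short postal questionnaire covers re-consultation. Those data could be subtracted, but only roughly: they are parents' reports set against practice records, they are abbreviated for postal responders, and they are missing for those who answer neither.

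Nor does it follow that a 14-day effect will show up as a significant one-year result. It moves the expected estimate, and significance from it alone is unlikely.

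Finally, the primary analysis is untouched, and this is one secondary outcome among several. That limits the weight of the point. It is not a matter to be left to a fuller document, because the article itself states the window and the data request.

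**Conclusion.** The point holds as a limit on interpretation. The one-year count is sound as a measure of total RTI consulting, but it does not isolate consulting after the index illness, so it cannot alone support the Conclusion's statement on medicalisation or the Discussion's on similar illness. At the planned effect, the expected count falls by at least 0.10 per child with no later change: about 5-10% on an assumed yearly mean of 1-2, and 3-14% over assumed later means of 3 down to 0.5. The chance that this alone gives a significant reduction is about 6-24%.

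The overlap follows from the stated windows and needs no assumption beyond same-illness visits being recorded as RTI consultations. Its size rests on the full 20% to 10% effect, equal visits per re-consulting child in the two arms, and a yearly mean and variance that the documents do not give. A smaller 14-day effect shrinks the shift in proportion.

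**What to change.** Ask practices for two RTI counts per child: days 1-14 after recruitment, and day 15 to one year. Keep their sum as the measure of overall burden. State in the plan that any conclusion about later consulting rests on the day-15-onward count.

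The study team already sends each child's start and end dates, so the cost is one more date boundary, one extra field per child and one sentence of definition. The days 1-14 count would also give a check from practice records on the parent-reported primary outcome.

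The limitation is that a calendar cut only approximates the illness episode. Same-illness visits after day 14 would fall in the later count, and a new illness within the fortnight would fall in the earlier one. The report should say so.

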### Potentially discardable pilot

We conducted a pilot study using two practices in South-East Wales. Both are group practices in areas of high socio-economic deprivation. These practices were randomly assigned by the study statistician, one to intervention and one to control. Recruitment and data collection processes were piloted and participating clinicians provided feedback on these processes and the on-line training. In addition, those clinicians who were in the intervention practice provided feedback on use of the intervention. Minor amendments were made to the on-line training as a result of this experience. As there were no major changes required, data from the pilot practices will be included in the main trial.

### Analysis

Statistical analyses will be conducted using SPSS, STATA, and MLwiN. The primary analysis will be intention to treat and will compare the proportion of patients who re-consulted for the same illness during the fourteen days following recruitment, in the intervention and control arms of the study. A two-level logistic model will be fitted to account for individual and practice-level factors.

Secondary outcomes include: proportion reporting having received a prescription for an antibiotic, proportion reporting having used antibiotics, parental enablement, parental satisfaction, parental assessment of the usefulness of any information received in the consultation, perceived reassurance, and the number of consultations for respiratory tract infections over the following year. These will be analysed using either two-level logistic or linear regression models as appropriate.

We will explore whether a three-level model to control for practitioner factors improves the fit of the model for each analysis.

No formal sub-group analyses are planned. However, exploratory analyses will be conducted of the impact of child's age, presenting symptom complex, and socio-economic background (using postcode of residence) on the effectiveness of the intervention.

### Process evaluation

We will conduct a qualitative process evaluation which will be reported in detail elsewhere. The purpose will be to gain a greater understanding of the clinicians' and parents' perceptions of the intervention (booklet and training) and the elements of it that were perceived to be helpful, and those which were unhelpful. A purposive sample of parents and clinicians in the intervention arm will be invited to participate in semi-structured interviews. These will be conducted between one and four months after enrolling in the study for the parents, and after completion of recruitment for the clinicians.

## Discussion

This will be the first study to explore the impact of using an interactive booklet on respiratory tract infections in children, designed for use within consultations, on re-consultations and antibiotic prescribing. Our intervention has been designed primarily for use with parents, although it could easily be understood by many older children, and acts as an aide-memoir for primary care clinicians. It is applicable to a wide range of childhood respiratory tract infections. The interactive booklet is more likely to be used, understood, and believed, if it is seen to be endorsed by the parent's primary care clinician. Clinicians using the intervention will be provided with training in its use that encourages them to endorse the booklet, to identify and highlight relevant sections of the booklet, and to use it as a prompt to improve communication within the consultation.

The Medical Research Council and others have recommended that complex interventions are based on a theoretical framework [55]. Our intervention is grounded in Social Cognitive Theory and the Theory of Planned Behaviour. Understanding the theoretical underpinnings of the intervention will help us explore which components of the intervention contributed to the effectiveness or lack of effectiveness of the intervention, and will aid in the implementation of the intervention if it is found to be effective [56].

### Outcome measures

Re-consultation for the same illness during the fourteen days following enrolment was chosen as the main study outcome for a number of reasons. Our previous studies have shown nearly one in five children re-consult for the same illness episode [4] Worried parents should not be discouraged from consulting. However, when a significant proportion of parents who have consulted feel the need to re-consult for the same illness, it suggests that they are not being empowered to self-manage these illnesses. Small reductions in resource use in common conditions could result in large savings on a national level. Finally, clinicians are likely to perceive greater pressure to prescribe antibiotics for children who seen for a second or third consultation for the same illness episode.

In addition to other 'clinical' or 'process' outcomes such as antibiotic prescribing and consultations for similar illness over the following year, we will also examine patient-related outcomes including parent reported satisfaction, reassurance, value of information received, and enablement. Enablement is a concept developed by Howie and colleagues which is related to, but different from satisfaction [54] The concept draws on the themes of patient centeredness and empowerment, and on the patient's perceived changes in understanding, coping, and confidence. We adapted the Patient Enablement Instrument for use with parents about care of their children. This involved mainly minor changes to the wording, but did require the item examining impact of the consultation on "ability to cope with life" to be dropped, as this seemed inappropriate when talking about a consultation regarding a third party (the child). No formal validation of this adaptation was conducted. However, its use was found to be acceptable in the pilot.

We will also measure potential adverse effects from the intervention. One UK study randomised 120 parents of infants in a single practice to receive a booklet on childcare followed by a visit from a health visitor, or usual care [57] There was no impact on use of healthcare services, and parents in the intervention arm reported lower levels of feeling confident and knowledgeable than in the control arm. We will measure parental enablement, satisfaction and reassurance, as well as serious adverse outcomes such as complications and hospitalisations.

### Design issues

One central issue relevant to the selection of study design was whether to conduct an efficacy or an effectiveness evaluation. A narrowly defined, closely controlled trial may have allowed us to show an effect that would not be shown in a pragmatic trial. However, such a trial would need to be followed by a further pragmatic trial to show whether the intervention is effective 'in real life general practice'. We have therefore decided to use a pragmatic trial design with broad inclusion criteria. We excluded children under six months of age because symptoms can be more difficult to interpret in very young children, and younger children have higher rates of complications [58]. Children over fourteen years of age were excluded because older children are less likely to consult [3] and be prescribed antibiotics [16]. A disadvantage of a pragmatic approach is an inability to control fidelity of intervention delivery, and this may result in an underestimation of any effect. We will however attempt to gain an understanding of how and whether the intervention was used through the process evaluation.

A further key decision regarding the design of the trial was whether to use an individually or cluster randomised design. Individually randomised trials are generally preferred because cluster trials suffer from a loss of power due to clustering effects. However, since the intervention in this case involves not just the booklet, but a change in the process of the consultation, an individually randomised trial would result in a risk of contamination of intervention delivery. It is not feasible for a clinician who has received training in using the booklet and communicating within the consultation, and has discussed the booklet with some parents, to switch between using this approach and 'usual care' at random.

The use of a cluster design can lead to selection bias at either the level of cluster or the individual. Practices who agree to take part in the study may find that they no longer wish to participate, leading to attrition bias. This would be of greater concern if there is differential drop-out of practices; for example if practices randomised to the control arm are less likely to recruit (resentful demoralisation). We aim to minimise attrition by maintaining regular contact and providing encouragement to all randomised practices, and will monitor and report on the attrition of clusters. Selection bias can also occur in cluster randomised trials where those who are recruiting participants are aware of the allocation given to their cluster [59]. We are not able to blind practices to their allocation as their use of the booklet within the consultation forms part of the intervention. We have attempted to minimise the risk of selection bias by asking practices to recruit sequential eligible patients, and we are trying to measure any selection bias by asking practices to record non-identifiable data on all 'potentially eligible' patients (i.e. all patients who have been given an information sheet about the study, including those who are deemed ineligible, do not consent, or are not recruited for other reasons).

### Other potential sources of bias

Outcomes will be measured primarily through a telephone-administered questionnaire at two weeks. It will not be possible to ensure that the interviewer remains completely blinded to study arm due to the possibility of participants discussing receipt of a booklet during their consultation. However, in order to minimise the risk of information bias, interviewers will not have any information about allocation, and questions will be devised to minimise the chance of participants disclosing which group they are assigned. If a participant discloses their allocation, the interviewer will record this so that these participants can be compared to those in which the interviewer remains blinded to allocation.

Similarly, it was not possible to blind participants to grouping. A 'placebo' booklet was considered. However, use of any booklet is likely to change a consultation, and we wish to assess effectiveness. In order to minimise reporting bias, participants will not be provided with specific information about the intervention or the outcomes being measured. Instead, information sheets state that the study team is interested in determining whether, "the type of information, and the way in which a primary care clinician (GP or practice nurse) communicates this information, can have an effect on your child's illness and the ways in which you deal with it."

### Use of web-based training

A novel aspect of our study will be the use of the Internet to provide training for practices. A clear advantage of this approach is that it precludes the need for a practice visit by the study team, and therefore makes recruitment of practices over a large geographical area possible. In addition, providing training on-line allows clinicians to complete the training at a time and place of their choosing, and at their own pace. Disadvantages of this approach include the time and cost of developing the training; we produced videos, recorded audio-clips, and developed shockwave animated objects for inclusion on the site. Other problems include the loss of face-to-face contact with clinicians, which is likely to have an impact on recruitment, and challenges in measuring training process and outcomes. With regard to the latter, because each clinician is provided with a unique log-in password, we will be able to monitor which pages they access and the amount of time spent accessing the site. This, in addition to written feedback which is requested from all users, will provide us with a measure of amount of training accessed, and their opinions of it.

## Conclusion

This study aims to evaluate the effect of a booklet developed specifically for use within consultations involving children with RTIs, on re-consulting for the same illness episode and antibiotic prescribing. We will determine whether changes in antibiotic use and re-consultation are achieved at the expense of patient satisfaction, and will determine whether the interactive booklet enhances patient enablement. We will evaluate the effect on medicalisation over the subsequent year. If this intervention is found to be effective, even small changes for the commonest acute consultation could have major effects on help seeking behaviour and free up consultations in primary care for other conditions. If not effective, resources spent on developing, printing, and distributing leaflets and booklets on respiratory tract infections in children can be re-directed, and the research agenda can be re-focussed. We believe that this is the first evaluation of the use of written material on respiratory tract infection in children during the consultation.
